# 12 Participant timelines

| Investigations | Baseline | At schedule visit | Progression |
| --- | --- | --- | --- |
| History | √ | √ | √ |
| Drug allergy | √ | X | X |
| Local examination | √ | √ | √ |
| CECT neck + relevant part | X | * | * |
| PET-CT | √ | X | X |
| Toxicity assessment | X | √ | √ |
| Biopsy / FNA | X | X | √ |
| CBC | √ | √# | √ |
| RFT | √ | √# | √ |
| LFT | √ | √# | √ |
| SE ,Ca, Mg | √ | √# | √ |
| TSH | √ | * | * |
| ECG | √ | X | X |
| b-HCG | √ | X | X |
| FACT -H&N QOL | √ | √ | X |
| Blood sample 10 Ml ( 5 ml EDTA + 5 ml Plain) | √ | √*** | √ |

**Table 3 : Timeline for participants in Arm : A**

***- CECT neck + scan of the relevant part would be done in accordance with the institutional standards.**

**#-Investigations will be done as per institutional standards and sos**

****- FACT H&N QOL would be collected at 6, 12,18,24 & 36 months from start of chemotherapy**

******- Blood sample will be collected only at the first 3 month visit.**

| Investigations | Baseline | D1 of chemotherapy for 18 cycles ( every 3 month in till 18 months) | Post 18 months at schedule visit | Progression |
| --- | --- | --- | --- | --- |
| History | √ | √ | √ | √ |
| Drug allergy | √ | X | X | X |
| Local examination | √ | √ | √ | √ |
| CECT neck + relevant part | X | * | * | * |
| PET-CT | √ | X | X | X |
| Toxicity assessment | X | √ | √ | √ |
| Biopsy / FNA | X | X | X | √ |
| CBC | √ | √ | √# | √ |
| RFT | √ | √ | √# | √ |
| LFT | √ | √ | √# | √ |
| SE ,Ca, Mg | √ | √ | √# | √ |
| TSH | √ | * | * | * |
| ECG | √ | √ | X | X |
| b-HCG | √ | X | X | X |
| FACT -H&N QOL | √ | ** | X | X |
| Blood sample 10 Ml ( 5 ml EDTA + 5 ml Plain) | √ | √*** | X | √ |

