## 10.2 Arm A

In arm A **observation** would be done. The schedule of observation will be in accordance with the institutional follow up protocol which is as below

**First year** : Patient would be followed up at 3 monthly intervals. Clinical history and examination would be done. Blood investigations like complete hemogram, renal function tests and TSH would be done. FACIT QOL H&N would be filled at baseline,6 and at 12 months. The blood of patients of 10 ml would be collected at baseline, first follow up and at progression in both arms for future research purpose

**Second year** : Patient would be followed up at 3 monthly intervals. Clinical history and examination would be done. Blood investigations like complete hemogram, renal function tests and TSH would be done sos. FACIT QOL H&N would be filled at 18 & 24 months

**Third year-Fifth year** : Patient would be followed up at 6 monthly intervals. Clinical history and examination would be done. Blood investigations like complete hemogram, renal function tests and TSH would be done sos.

**Post fifth year** : Patient would be followed up at 1 year intervals. Clinical history and examination would be done. Blood investigations like complete hemogram, renal function tests and TSH would be done SOS.

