### 10.3.1 Schedule

Metronomic chemotherapy is the study intervention in this trial. The metronomic chemotherapy constitutes of methotrexate and celecoxib.

Oral methotrexate tablet 15 mg/m2 will be self administered weekly ie on D1,D8, D15 and D22 of every 28 day cycle.

Capsule celecoxib would will be self administered twice daily in a dose of 200 mg BID continuously .

The combination will be continued to a maximum of such 18 cycles; unless prohibitive toxicity or disease progression occurs prior to it. The schedule of visits of these patients would be similar to that in observation arm. Except that ECG and LFT would be done at each visit.

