#### 10.3.3.1 Dose modification for hematological toxicity

| **PARAMETER** | **TIMING** | **RESULT OR PROBLEM** | **CTCAE GRADE** | **ACTION WITH STUDY TREATMENT**  **(Methotrexate unless otherwise specified)** | | | | |
| --- | --- | --- | --- | --- | --- | --- | --- | --- |
| Neutrophils  (x10^9^/L) | Previous cycle | Febrile neutropenia, or infection with neutropenia | G4 | Delay D1 until resolved AND  reduce dose of methotrexate by 20% | | | | |
|  |  |  |  |  |  |  |  |  |
|  | D1 | 1.0-1.5 | G2 | Delay D1 until ANC is >1.5 AND  If delay > 7 days but < 15days, reduce doses by 20% level.  If delay >15 days then discontinue. | | | | |
|  |  | <1.0 | G3-4 | Delay D1 until ANC is >1.5 AND  reduce doses by 20% level. | | | | |
| Platelets  (x10^9^/L) | Previous cycle | < 25 or bleeding | G4 | Delay D1 until resolved AND  reduce methotrexate doses by 20% | | | | |
|  | D1 | <100 | G1-4 | Delay D1 until platelet count is > 99 x10^9^/L AND  If delay > 7 d but <15 days reduce doses by 20% level.  If delay > 15d then discontinue. | | | | |
| Haemoglobin  (g/L) | First occasion | <80 | G2 | Transfuse to Hb > 80 g/L AND  treat as scheduled. | | | | |
|  | Second occasion | <80 | G2 | Transfuse to Hb >80, treat as scheduled, AND reduce doses of methotrexate by 20% | | | | |
| Day 1 treatment may be delayed for a maximum of 14 days. If the adverse event has not resolved to G0-1 after delaying day 1 treatment for 14 days, then chemotherapy should be discontinued.  **- No dose reduction in celecoxib recommended. However, if chemotherapy is discontinued then celecoxib should also be discontinued. | | | | |  |  |  |  |

Table 1 : Dose modification in hematological events

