### 10.3.4 Start of a new cycle

Re-treatment on day 1 will require: haemoglobin > 8 mg/dl, ANC count > 1500/mm3, platelet count > 1 lakh/mm3, creatinine clearance rate >30 ml min, and resolution of all non haematological toxicities (except alopecia and fatigue) to baseline or less than grade 1.

If methotrexate is delayed or withheld and if the cause of the delay does not require an interruption in celecoxib then it will be continued. Subsequently methotrexate can be given on the next weekly scheduled day. The scheduled methotrexate which was omitted remains omitted. The cycle would be considered continued if celecoxib is continued. If both are delayed and the delay is less than 15 days then from the day of restart the remaining cycle would be completed.

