**Table 4 :Timeline for participants in Arm : B**

***- CECT neck + scan of the relevant part would be done in accordance with the institutional standards.**

**#-Investigations will be done as per institutional standards and sos**

****- FACT H&N QOL would be collected at 6, 12,18,24 & 36 months from start of chemotherapy**

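### Arm B's day-1 rules need blood results before every 28-day cycle, but the visit schedule can be read as supplying them only every 3 months

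*Protocol*

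**What the plan says.** **The day-1 rule.** Section 10.3.4 states: "Re-treatment on day 1 will require: haemoglobin > 8 mg/dl, ANC count > 1500/mm3, platelet count > 1 lakh/mm3". It adds a creatinine clearance above 30 ml/min and recovery of non-haematological toxicity. Table 1 (section 10.3.3.1) ties delay, 20% dose reduction, transfusion and discontinuation to neutrophils, platelets and haemoglobin. Section 10.3.1 sets a 28-day cycle, weekly self-administered methotrexate and at most 18 cycles.

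**The schedule.** In Table 4 (section 12) the on-treatment CBC and RFT sit in one column, headed "D1 of chemotherapy for 18 cycles ( every 3 month in till 18 months". Section 10.3.1 says of Arm B: "The schedule of visits of these patients would be similar to that in observation arm", and then: "Except that ECG and LFT would be done at each visit". For the observation arm, section 10.2 says of both the first and the second year: "Patient would be followed up at 3 monthly intervals". CBC and RFT are plain ticks in Table 4 during treatment. After month 18 they carry a # mark, explained as "Investigations will be done as per institutional standards and sos".

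**The thresholds.** Section 10.3.4 gives the haemoglobin limit in mg/dl, Table 1 uses 80 g/L, and section 11.1 uses g/dl. The neutrophil row of Table 1 ends: "If delay >15 days then discontinue", and the platelet row has the same limit. The Table 1 footnote and section 10.3.3 allow at most 14 days' delay. Section 10.4 discontinues for a treatment-related delay of 14 days.

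**The concern.** A day-1 rule works only if a result is available on day 1. The rule runs on a 28-day clock. The schedule from which tests are booked can be read as running on a 3-month clock, and no other section provides blood tests between visits.

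On the 3-monthly reading, a fall in counts without symptoms could pass through several cycles without triggering the hold, reduction or transfusion that Table 1 prescribes. Clinical triggers such as febrile neutropenia or bleeding would still apply. The frequency of holds and reductions would also depend on which reading was followed. The stake is the safety and uniform conduct of the experimental arm.

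The two threshold errors matter less, but they sit in the rules that decide whether a patient is re-treated or permanently stopped.

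**Working it through.** The plan gives no figure of its own here, so the check sets cycle dates against visit dates.

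**1. Decisions needing a count.** Cycle k starts on day 28 × (k − 1). Cycles 2 to 18 start on days 28, 56, …, 476, which gives 17 decisions. Cycle 1 is covered by the baseline tests.

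**2. Per-cycle reading.** All 17 starts have a scheduled count: 17 − 17 = 0 uncovered.

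**3. 3-monthly reading, no cycle delay.**
- Best case for overlap, a visit every third cycle (84 days): days 84, 168, 252, 336 and 420 coincide with cycle starts. The next visit, day 504, falls after the last start on day 476. Covered: 5. Uncovered: 17 − 5 = 12, and 12/17 = 71%.
- Calendar quarters (about 91.3 days): visits fall on days 91, 183, 274, 365 and 457, again 5 by day 476, so at most 5 decisions can be covered. Only three of the 17 starts (days 84, 280 and 364) lie within 7 days of a visit.
- At least 12 of 17 are therefore uncovered on this reading.

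**4. Weekly doses between scheduled counts.** 84/7 = 12; 91.3/7 = 13.0.

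**5. Which reading the text favours.** Section 10.3.1 and the parenthesis in the Table 4 heading point to 3-monthly. Section 10.3.4, Table 1 and the grading of adverse events after each cycle (section 11.2) point to per cycle. The text does not settle it.

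**6. Haemoglobin unit.** 8 mg/dl × 10 = 80 mg/L = 0.08 g/L. Table 1 has 80 g/L, and 80/0.08 = 1000. As printed, the limit would hold nobody back.

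**7. Length of delay for a neutrophil or platelet event.**

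| Delay | Table 1 rows | Table 1 footnote and 10.3.3 | 10.4 |
| --- | --- | --- | --- |
| 13 days | reduce, continue | delay allowed | continue |
| 14 days | reduce, continue | last day allowed | discontinue |
| 15 days | no action given | discontinue | discontinue |
| 16 days | discontinue | discontinue | discontinue |

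The sources disagree only at 14 and 15 days. Section 10.3.4, which lets an interrupted cycle resume when both drugs were delayed for under 15 days, fits a 14-day maximum.

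**The case against.** **The heading need not contradict itself.** A reader might infer that its two halves cannot both hold. They can, if visits fall on day 1 of every third cycle during the treatment period, and that also agrees with sections 10.3.1 and 10.2. This stands. What remains is a gap between section 10.3.4 and the schedule.

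**Section 10.3.4 is unconditional.** A visit table does not waive a required test, so the document does not show that patients will be re-treated unchecked, or that practice will differ between patients from TMH and ACTREC, who come under one department (section 8). This also stands. The defect is that a mandatory test has no clearly scheduled occasion.

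**Larger and smaller counts.** A reader might carry over section 10.2's second-year rule, "Blood investigations like complete hemogram, renal function tests and TSH would be done sos", and reach 13 of 17 (76%). The plain on-treatment ticks in Table 4 exclude that. A reader might also reach 11 of 17 (65%) by letting delays bring a sixth visit, on day 504, onto a cycle start. That needs at least 504 − 476 = 28 days of total delay with both drugs interrupted, because section 10.3.4 counts the cycle as continuing while celecoxib is taken.

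**The threshold errors are small.** The haemoglobin unit is plainly a slip, and Table 1 shows what was meant. A reader might say that nothing is prescribed at 15 days; the rows are silent there, but the footnote, which is part of Table 1, discontinues. Both remarks are fair, and both errors still deserve correction.

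**The regimen appears mild.** Section 4.6 reports no grade 3-4 toxicity in the retrospective methotrexate and celecoxib series. That lowers the expected harm. The protocol nevertheless sets haematological and renal limits, and these need results to act on.

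**Conclusion.** The concern holds as a gap between a mandatory per-cycle rule and a schedule that does not clearly serve it. Its size depends on the reading: 0 of 17 decisions without a scheduled count if Table 4 means every cycle, and at least 12 of 17 (71%) if it means every 3 months, with about 12 to 13 weekly doses between counts. The second figure assumes all 18 cycles are given, no interruption of both drugs long enough to shift the calendar, and no unscheduled tests.

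The haemoglobin unit and the 14- versus 15-day limits are minor threshold errors. The second affects only delays of 14 or 15 days.

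A reader might infer an effect on the trial's main result. Nothing here bears on the survival analysis, alpha or power. The correction should be made because it is cheap and concerns the safety rules of the experimental arm.

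**What to change.** 1. **Schedule.** In Table 4 and section 10.3.1, state that CBC and RFT (local laboratory allowed), with a brief toxicity check that may be remote, are done before day 1 of each of cycles 2 to 18 and repeated during any delay. The toxicity check is needed because section 10.3.4 also requires non-haematological recovery. Clinic visits, ECG and LFT stay 3-monthly, so the on-treatment column of Table 4 is best split in two.
2. **Haemoglobin.** In section 10.3.4 write 8 g/dl (80 g/L).
3. **Delay.** Use one limit throughout: in the neutrophil and platelet rows of Table 1 change more than 15 days to more than 14 days, and in section 10.4 discontinue for a treatment-related delay of more than 14 days. Changing Table 1 alone would leave the conflict at exactly 14 days.

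**Cost.** Items 2 and 3 are wording only. Item 1 adds up to about 12 local blood draws per Arm B patient completing 18 cycles, plus the brief checks, all of which section 10.3.4 already implies. As an upper bound, assuming 1:1 allocation of the 1038 patients in section 13.3.1 and full treatment for all, that is 519 × 12 = 6,228 draws over the trial. Endpoints, sample size, randomization and clinic visits do not change.

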### 6.2.2 Secondary objectives

1. To compare the 3 year progression free survival of adjuvant metronomic chemotherapy with that of observation in patients with locally advanced head and neck cancers post radical chemoradiation . The secondary endpoint would be 3 year progression free survival.
2. To compare the grade 3-4 toxicity between adjuvant metronomic chemotherapy and observation
3. To compare the 6,12,18,24 & 36 months QOL scores between the 2 arms

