# 9 Eligibility criteria

## 9.1 Inclusion criteria

1. Participants must be post radical chemoradiation for a histologically confirmed stage III-IV squamous cell cancers of the head and neck region.
2. Participants must have no gross residual disease post of completion of CTRT
   1. Assessment for same would be done in accordance with institutional standards at a visit post 10-12 weeks of completion of CTRT by PET CT
3. Participants must have malignancy arising from one of the following sites pharynx ( inclusive of oropharynx, hypopharynx) or larynx ( inclusive of supraglottis, glottis and subglottis).
4. Age : Any age above 18 years. No maximum age.
5. ECOG performance status ≤2
6. Participants must have normal organ and marrow function as defined below:
   1. Leukocytes ≥3,000/mcL
   2. Platelets ≥100,000/mcL
   3. Total bilirubin < 1.5 × institutional upper limit of normal
   4. AST(SGOT)/ALT(SGPT) ≤2.5 × institutional upper limit of normal
   5. Calculated Creatinine clearance > 30 ml/min
7. The effects of oral metronomic chemotherapy ( inclusive of methotrexate) on the developing human fetus are teratogenic. Hence women of childbearing potential and men must agree to use adequate contraception (hormonal or barrier method of birth control; abstinence) prior to study entry and for the duration of study participation. Should a woman become pregnant or suspect she is pregnant while she or her partner is participating in this study, she should inform her treating physician immediately. Men treated or enrolled on this protocol must also agree to use adequate contraception prior to the study, for the duration of study participation, and 6 months after completion of protocol.
8. Both men and women of all races and ethnic groups are eligible for this trial.
9. Willing and able to comply with all study requirements, including treatment (able to swallow tablets), able to be followed up at regular intervals and/or nature of required assessments (e.g. able to have IV contrast if this is required for tumour assessments)
10. Ability to understand and the willingness to sign a written informed consent document

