## 9.2 Exclusion Criteria

1. Participants who are receiving any other investigational agents.
2. Primary sites of malignancy in oral cavity or major salivary gland or nasopharynx or skin
3. More than Six months post completion of CTRT
4. Patients with QTc prolongation defined as QTc interval greater than 480 ms in view of risk of sudden cardiac death associated with use of celecoxib.
5. Patients receiving methotrexate for other indications not limited to rheumatoid arthritis
6. Patients who had received long term Cox-2 inhibitors ( more than 3 month continuous usage) will be excluded
7. History of allergic reactions attributed to compounds of similar chemical or biologic composition to any agents used in study.
8. Uncontrolled intercurrent illness including, but not limited to, hypertension, tuberculosis, diabetes, ongoing or active infection, symptomatic congestive heart failure, unstable angina pectoris, cardiac arrhythmia, renal failure (on dialysis), active gastrointestinal bleeding, cerebrovascular accidents, inflammatory bowel disease, known hyperkalemia ( CTCAE version 4.02 grade 3 or above which is persistent over 1 week) or psychiatric illness/social situations that would limit compliance with study requirements.
9. Pregnant women and breastfeeding women are excluded from this study because celecoxib / erlotinib and methotrexate are agents with the potential for teratogenic or abortifacient effects. Because there is an unknown but potential risk for adverse events in nursing infants. These potential risks may also apply to other agents used in this study.
10. HIV-positive, Hepatitis B and C seropositive patients are excluded from this study.
11. Patients with previous history of other cancers within last 2 years

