## 11.2 Secondary outcomes

1. 3 year PFS : PFS will be defined time in days between date of randomization to date of progression or death whichever is earlier. Patients who have not progressed or died at their last follow ups would be censored.The 3 year PFS would be estimated by Kaplan meier analysis and would be compared between the 2 arms by the log rank test. Cox proportional hazard model would be constructed for calculation of hazard ratio. The model would also be used to see the impact of chemotherapy regimen on 3 year progression survival in accordance with known prognostic factors. Age ( below or above 70 years), subsite , T stage, N stage, hemoglobin level ( equal to or below 10 g/dl or above it), and PS ( 0-1 versus 2).This information would be depicted in the form of a forest plot.
2. Toxicity : To compare CTCAE version 4.03 worst grade toxicity between the 2 arms during any period of chemotherapy. Chi- square test or fisher's test would be used for comparison. The NCI Common Terminology Criteria for Adverse Events version 4 (NCI CTCAE v4.03) will be used to classify and grade the intensity of adverse events after each treatment cycle. CTCAE will be used to collect all events regardless of attribution, in order to ensure objective reporting, and in order to report trial data according to accepted international guidelines. The worst toxicity would be recorded. The results would be computed in a tabular form in which the proportion of people having their highest grade of toxicity would be charted.
3. TOI ( Trial outcome index) : TOI will be calculated at baseline and at 6, 12,18,24 & 36months in both arms from FACT Head and neck QOL proformas. Increment in TOI of 6 units would be considered significant. Proportion of patients with significant improvement in TOI will be compared between 2 arms. Proportion test would be used for comparison.

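### No CTCAE grade is scheduled at baseline in either arm, so clinical toxicity left over from chemoradiation can be counted as on-study toxicity in the grade 3-4 comparison

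*Protocol*

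**What the plan says.** In Protocol section 12, Table 3 (Arm A) and Table 4 (Arm B) both show "Toxicity assessment | X" in the baseline column. Toxicity assessment is ticked at every later column. History, local examination, CBC, RFT, LFT, electrolytes, ECG and the FACT-H&N questionnaire are ticked at baseline in both arms.

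Section 6.2.2 makes toxicity a secondary objective: "To compare the grade 3-4 toxicity between adjuvant metronomic chemotherapy and observation". Section 11.2 defines the analysis: "To compare CTCAE version 4.03 worst grade toxicity between the 2 arms during any period of chemotherapy", and adds "CTCAE will be used to collect all events regardless of attribution, in order to ensure objective reporting".

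On timing of entry, section 9.1 places the qualifying response assessment "at a visit post 10-12 weeks of completion of CTRT by PET CT", and section 9.2 excludes patients who are "More than Six months post completion of CTRT".

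On starting a new cycle, section 10.3.4 asks for "resolution of all non haematological toxicities (except alopecia and fatigue) to baseline or less than grade 1". Section 10.3.3 states the general restart threshold as grade 0-1.

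**The concern.** The whole population has just finished radical head and neck chemoradiation. Beyond organ and marrow function, ability to swallow tablets and the absence of uncontrolled illness, no eligibility criterion asks that treatment toxicity has resolved. A worst-grade endpoint that ignores cause will pick up whatever is still present at the first on-study assessment. To remove it, one must know the grade at entry, and the schedule does not collect that grade for clinical toxicities.

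At stake is how well the trial can describe the added harm of 18 months of methotrexate and celecoxib. The concept sheet presents the regimen as minimally toxic and expects grade 3-4 side effects in fewer than 5% of patients. A signal of that size is easily blurred by a modest background. A later analysis plan can define what counts as new or worsened, but it cannot supply a grade that was never recorded. The primary endpoint, the sample size and the error rates are not affected.

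**Working it through.** **Is there an entry value?** The protocol states no toxicity rate or power to reproduce, so the first step is to set the sections side by side.

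- Liver, renal, electrolyte and blood count toxicities: the laboratory tests are ticked at baseline in both arms, so an entry grade can be derived.
- Mucositis, nausea, skin and other clinical toxicities: only ungraded history, local examination and a quality-of-life form. No CTCAE grade is scheduled.
- Adverse event reporting under section 18 does not fill the gap, because non-serious events need not be reported.

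**Size under equal capture (illustration).**

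Inputs: n = 519 per arm, from the 1038 in section 13.3.1 with 1:1 allocation assumed. New grade 3-4 toxicity of 2% in Arm A and 6% in Arm B (assumed). Carry-over prevalence b, equal in both arms (assumed, as the protocol gives none). Two-sided 5% test.

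Formulas:
- pA = 1 − 0.98(1 − b) and pB = 1 − 0.94(1 − b)
- power = Φ[(pB − pA − 1.96·s0)/s1], with s0 = √(2p̄(1 − p̄)/n), s1 = √([pA(1 − pA) + pB(1 − pB)]/n) and p̄ the mean of pA and pB

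For b = 0: s0 = √(2 × 0.04 × 0.96/519) = 0.01216 and s1 = 0.01210. Power = Φ[(0.04 − 0.02383)/0.01210] = Φ(1.34), about 91%.

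For b = 5%: s0 = 0.01759 and s1 = 0.01755. Power = Φ[(0.038 − 0.03448)/0.01755] = Φ(0.20), about 58%.

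| b | Arm A | Arm B | Difference | Relative risk | Power |
|---|---|---|---|---|---|
| 0% | 2.0% | 6.0% | 4.0 points | 3.00 | 91% |
| 5% | 6.9% | 10.7% | 3.8 points | 1.55 | 58% |
| 10% | 11.8% | 15.4% | 3.6 points | 1.31 | 39% |
| 15% | 16.7% | 20.1% | 3.4 points | 1.20 | 29% |

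The concept sheet gives 1046 patients instead of 1038. Using 523 per arm changes each power by less than half a percentage point.

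**Sensitivity to the assumed rates.** Take no other background, so that Arm A = b and Arm B = 1 − (1 − b)(1 − d), with d the drug-caused rate.

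- d = 5%: power falls from about 99.9% (b = 0) to 83%, 60% and 34% at b = 5%, 10% and 20%.
- d = 3%: power falls from 98% to 47%, 28% and 16%.

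The pattern is the same: the relative risk and the power drop sharply, and the absolute difference only slightly.

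**Unequal capture.** Table 4 heads its on-treatment column with day 1 of each of 18 cycles, then adds a 3-monthly qualifier. Section 10.3.1 says Arm B visits resemble those of the observation arm. Read literally, the heading puts an Arm B assessment on cycle 1 day 1, whereas section 10.2 sees Arm A at 3-monthly intervals. Sequelae that resolve in between would then be counted in Arm B only. For example, with a 2% new rate in both arms and no drug effect, suppose 10% carry-over is captured in Arm B and 5% in Arm A. The rates are 1 − 0.98 × 0.90 = 11.8% and 1 − 0.98 × 0.95 = 6.9%, an apparent excess of 4.9 points.

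**The case against.** Several points on the other side have force.

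1. **The re-treatment rule.** A reader might infer that sites cannot apply section 10.3.4 because it refers to an uncollected baseline. The protocol does not support that. The rule offers an alternative to baseline, section 10.3.3 uses an absolute threshold, and Table 2 mostly uses grade 0-1. Its baseline-relative entries are creatinine and AST/ALT, which have baseline tests. What remains is narrower: for clinical toxicities the word baseline has no graded value behind it, and the alternative in section 10.3.4, read literally as grade 0, does not match grade 0-1 in section 10.3.3.

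2. **Worsening rather than persistence.** Section 18 lists worsening of pre-existing illness among adverse events, so persistence alone may not count, and ignoring attribution concerns cause rather than timing. This is fair: section 11.2 does not say that leftover toxicity is scored as new. But worsening can only be judged against an entry grade, so this reading also needs the missing value.

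3. **Eligibility limits carry-over.** The bilirubin and transaminase limits rule out grade 3-4 hepatic toxicity at entry, uncontrolled or active infection is excluded, and patients must be able to swallow tablets. This stands, and it lowers the plausible carry-over. It does not remove it for mucosal or skin effects.

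4. **The magnitude is assumed.** Also true. In addition, randomisation balances carry-over in expectation, and the toxicity endpoint has no stated power target.

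5. **A definition of new or worsened toxicity may sit in the analysis plan.** That part may indeed be left there. The assessment schedule is the protocol's own.

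**Conclusion.** The point holds in limited form. Neither arm has a scheduled CTCAE grade before treatment. For clinical toxicities, therefore, leftover chemoradiation effects can enter a worst-grade comparison that disregards attribution, with no reliable way to remove them afterwards.

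The size is unknown, because the protocol gives no carry-over prevalence. Under the assumed 2% and 6% rates and equal capture, carry-over of 5% to 15% takes power from about 91% to between 58% and 29%, and relative risk from 3.0 to between 1.55 and 1.20. The absolute difference stays between 3.8 and 3.4 points against 4.0.

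A reader might infer that the harm of the study drugs is bound to be understated. That does not follow. The absolute difference is nearly preserved under equal capture, and an earlier first assessment in Arm B could overstate the harm instead. Nor does it follow that no baseline exists at all, since laboratory toxicities have one. This is a cheap improvement to a secondary safety endpoint.

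**What to change.** - **Section 12, Tables 3 and 4:** change the baseline toxicity cell from X to √, meaning a CTCAE v4.03 grade of each existing toxicity, recorded before randomisation in both arms.
- **Section 11.2:** compare grade 3-4 toxicity that is new or worse than the patient's entry grade, over the same time window in both arms. The window needs stating, since section 11.2 ties it to chemotherapy and Arm A receives none on study. Keep the uncorrected worst-grade table as descriptive.
- **Sections 10.3.3, 10.3.4 and 12:** reconcile what baseline means for re-treatment, and the two restart thresholds, with what the schedule collects. Which threshold should apply is a clinical decision for the investigators.

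The cost is one CRF page at a visit where history, examination and blood tests are already done. For patients already enrolled, entry grades would have to be taken from their notes, with the lower reliability that implies, or those patients would contribute only to the uncorrected table.
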